#### Primary outcome

3.9.1

##### Motor competence

3.9.1.1

Motor competence will be the primary outcome of the study and will be assessed using the MOBAK 5–6 (Motorische Basiskompetenzen) battery, validated for fifth- and sixth-grade elementary school children (38). This instrument assesses basic motor competence across two dimensions: self-movement (balance, rolling, jumping, and moving) and object movement (throwing, catching, bouncing, and dribbling).

Each dimension includes four motor tasks, which are scored dichotomously (0 = task not achieved; 1 = task achieved according to established criteria). Scores for each dimension range from 0 to 4 points, and the total score ranges from 0 to 8 points, with higher values indicating a higher level of motor competence.

#### Secondary outcomes

3.9.2

##### Physical fitness

3.9.2.1

Physical fitness will be assessed using standardized field tests. Cardiorespiratory fitness will be measured using the 6-min walk test, which is used to estimate maximum oxygen consumption (VO₂max) (39). Lower limb muscle strength will be assessed using the standing long jump test, while upper limb muscle strength will be assessed using a handgrip strength test with a dynamometer (Camry EH101), following validated protocols (40).

##### Body composition and morphological variables

3.9.2.2

Body composition will be estimated using an eight-electrode tetrapolar bioelectrical impedance analysis (InBody 570®) (41) to obtain indicators of fat mass and muscle mass.

Morphological variables will include body weight, height, body mass index (BMI), and waist circumference; measurements will be taken by an anthropometrist accredited by the International Society for the Advancement of Kinanthropometry (ISAK) Level II (42). The ISAK protocol consists of a standardized measurement technique that ensures reproducibility by first marking specific anatomical landmarks (e.g., acromial, radial, iliac) and taking duplicate measurements (or triplicate if the difference exceeds 5%). A calibrated anthropometric kit (skinfold caliper, metal tape measure, and anthropometer) will be used to ensure that the technical error of measurement (TEM) is less than 1% for waist circumference.

##### Physical activity level (target)

3.9.2.3

Physical activity levels will be objectively assessed using triaxial accelerometry (ActiGraph wGT3X-BT, Pensacola, FL, USA) (43). Following the RENUÉVATE Specific Monitoring Protocol, the devices will be placed on the right hip using an adjustable elastic belt, ensuring their stability during multidirectional movements.

In accordance with the study’s central objective, to evaluate the pedagogical efficacy of alternative sports, the accelerometers will be used exclusively during Physical Education sessions (90 min). The research team will personally supervise the placement at the start and removal at the end of each class during the 8-week intervention. This methodological decision allows for rigorous control of the physical activity dose strictly linked to the pedagogical model (TGfU vs. Traditional), minimizing statistical noise from extracurricular activities.

The devices will be configured with a sampling rate of 30 Hz, and data will be processed in 15-s epochs, optimizing the capture of the intermittent nature of children’s movement (44). Non-use time will be defined as ≥20 consecutive minutes of zero counts. To ensure data validity, a session will be considered valid if it records at least 80% of the total class time, thereby ensuring an accurate representation of motor behavior during the intervention.

The intensity of physical activity will be categorized using the intensity thresholds (cut-off points) validated by Evenson et al. (45) for the pediatric population, due to their high accuracy in classifying activity levels in school settings. Data will be classified according to the following counts per minute (cpm) ranges: Sedentary: 0–100 cpm; Light physical activity (LPA): 101–2,295 cpm; Moderate physical activity (MPA): 2296–4,011 cpm; Vigorous physical activity (VPA): ≥4,012 cpm.

The primary movement variable, moderate-to-vigorous physical activity (MVPA), will be obtained by summing the time recorded in the moderate and vigorous categories. This indicator will allow us to quantify compliance with international health recommendations and determine the actual impact of the pedagogical model on students’ energy expenditure during class.

##### Physical activity level (self-reported)

3.9.2.4

The Youth Activity Profile (YAP-LA) (46) is a self-report questionnaire consisting of multiple items with responses on a five-point Likert scale that assesses physical activity and sedentary behavior during school and after-school hours over the previous 7 days. Composite scores are calculated according to the standardized scoring protocol, where higher scores indicate higher levels of physical activity.

##### Enjoyment of physical activity

3.9.2.5

Enjoyment of physical activity will be assessed using the Physical Activity Enjoyment Scale (PACES), validated in school-aged populations (47). The scale consists of 16 items rated on a five-point Likert scale that assess positive and negative affective responses associated with participation in physical activity. Negatively worded items will be reverse-coded, and a total score will be calculated, where higher values indicate greater enjoyment.

##### Sociodemographic variables and covariates

3.9.2.6

Sociodemographic variables will be collected via a questionnaire completed by parents or legal guardians, including educational level, household income, and family structure. These variables will be used to characterize the sample and will be considered covariates in the statistical analyses.

### Reliability thresholds and control of technical error of measurement

3.10

Prior to the start of fieldwork, a pilot study will be conducted with approximately 10% of the total sample to assess the reliability of all anthropometric, physical, and questionnaire-based measurements included in the study. This pilot phase will allow for the verification of measurement accuracy and the standardization of assessment procedures prior to data collection.

For continuous variables, the following reliability indicators will be calculated: absolute TEM, relative TEM (%TEM), coefficient of variation (CV%), and intraclass correlation coefficient (ICC) with 95% confidence intervals. Acceptable reliability thresholds will be defined as follows: %TEM ≤ 0.5% for height and body mass, and ≤1% for circumferences (intra-rater reliability). For performance-based physical fitness tests, a CV ≤ 3% will be required for speed and agility tests, and a CV ≤ 5% for jump-based tests.

For self-report instruments, test–retest reliability will be assessed using the ICC, calculated over a retest interval of 7 to 14 days, with ICC values ≥0.70 considered acceptable. Internal consistency will be assessed using Cronbach’s alpha, with values ≥0.70 indicating adequate reliability.

If any rater fails to meet the predefined reliability criteria, they will be provided with additional training, and the measurements will be repeated until acceptable thresholds are reached. All reliability indicators (TEM, %TEM, CV%, and ICC with 95% confidence intervals) will be included in the final publication, and sensitivity analyses will be performed when appropriate.

#### Quality assurance of measurements

3.10.1

All anthropometric and physical fitness assessments will be performed by assessors who have been previously trained and standardized by the research team. To ensure measurement quality during the main study, inter-rater reliability will be assessed in a random subsample comprising approximately 10% of the participants.

Inter-rater reliability will be estimated using ICC and TME. Acceptable thresholds will be defined as a TME < 2% for anthropometric variables and <5% for physical fitness tests, in accordance with established methodological recommendations (48). These procedures will ensure consistency among assessors and maintain the quality and reproducibility of measurements throughout the data collection process.

### Ethics and dissemination: research ethics approval, consent, and confidentiality

3.11

This study protocol was designed and will be conducted in accordance with the ethical principles established in the Declaration of Helsinki and with current ethical regulations for research in physical activity and health sciences involving school-aged populations. The study was reviewed and approved by the Scientific Ethics Committee of the Universidad Católica del Maule, Chile (No. 112/2025, approved on July 3, 2025).

Before the intervention begins, the parents or legal guardians of participating students will receive detailed and understandable information about the study’s objectives, the procedures involved, the potential benefits and risks, and the voluntary nature of participation. Next, written informed consent authorizing the students’ participation will be obtained. In addition, students will provide their informed consent, expressing their willingness to participate in the study, prior to the administration of any assessment or intervention.

Confidentiality and the protection of personal data will be ensured throughout all phases of the study. The collected data will be coded and stored securely, and access will be restricted exclusively to the research team. Under no circumstances will the data be used for purposes other than the scientific and academic objectives defined in the protocol. The study results will be analyzed and reported in aggregate form, ensuring the confidentiality and anonymity of all participants. The information obtained will be used solely for scientific, academic, and knowledge-advancement purposes in the field of physical education.

### Data management, access, and dissemination policy

3.12

Data collection will be conducted at the participating educational institutions, following the standardized procedures defined in the study protocol. This process will be carried out by a team of trained research assistants who will be responsible for administering the assessment instruments and recording the initial data.

The collected data will be transferred to the principal investigator and the co-investigator, who will oversee the review, organization, and secure storage of the data. All information will be stored in password-protected digital databases, and a backup copy will be saved in a secure Google Drive folder, with access restricted exclusively to the research team. Subsequently, the cleaned datasets will be exported to statistical software for analysis, and access to these data will be limited to the researchers responsible for the study.

Once the anonymization procedures are complete, the de-identified datasets may be shared with collaborating researchers or peer reviewers upon reasonable request and solely for scientific purposes, through controlled access to a digital repository, always ensuring the confidentiality and privacy of the participants.

The study results will be disseminated both nationally and internationally. National dissemination will include academic and scientific outreach activities, such as seminars, webinars, and institutional educational platforms. Internationally, the results will be presented at scientific conferences and submitted for publication in indexed, peer-reviewed journals related to physical activity, health, and education.

### Statistical analysis

3.13

#### Descriptive analysis

3.13.1

The baseline characteristics of the participants will be described using descriptive statistics. Continuous variables will be summarized as means and standard deviations or medians and interquartile ranges, as appropriate, after assessing the data distribution using the Kolmogorov–Smirnov test and visual inspection. Categorical variables will be presented as frequencies and percentages.

#### Primary analysis (intention-to-treat)

3.13.2

The primary analysis will be conducted according to the intention-to-treat (ITT) principle, including all participants as they were originally assigned, regardless of their adherence to the intervention. To estimate the effects of the RENUÉVATE intervention, mixed-effects regression models will be used to adequately account for the cRCT design (students nested within schools).

The effects of the intervention will be assessed through the group × time interaction, which represents the differences between groups in changes from baseline (Session 1) to post-intervention (Session 16). For continuous outcomes, including motor skills, physical fitness, enjoyment, physical activity levels, and body composition, linear mixed-effects models will be applied. For dichotomous outcomes, where applicable, generalized linear mixed models (GLMM) with a logit link function will be used.

All models will include group (intervention vs. control), time (baseline and post-intervention), and their interaction as fixed effects. Age and sex will be included as covariates. A random intercept will be specified for school to account for intraclass correlation within clusters.

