### Procedures, outcome measures, and data collection

3.9

Assessments will be conducted at two time points: at baseline, prior to the start of the intervention (Session 1), and at the end of the program (Session 16). At both time points, anthropometric measurements, physical fitness, motor competence, objectively and subjectively assessed physical activity levels, and enjoyment of physical activity will be collected.

Data collection will be carried out by a team of trained research assistants, who will receive prior instruction from the research team through specific training sessions designed to ensure the correct application of the assessment instruments and the standardization of procedures. The evaluators will have no prior relationship with the students, and their role in the study will be limited exclusively to data collection, in order to minimize any potential bias in the evaluation.

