#### Effect estimates and statistical inference

3.13.4

Results will be presented as adjusted between-group differences in change, with corresponding 95% confidence intervals (CI). Statistical significance will be set at *p* < 0.05 (two-sided). Standardized effect sizes will be calculated using Cohen’s d, based on adjusted estimates derived from mixed-effects models, to facilitate interpretation of the magnitude of the intervention effects.

All statistical analyses will be performed using SPSS version 28.0 (IBM Corp., Armonk, NY, USA) and R version 4.3, employing the lme4 package for mixed-effects modeling and the GGIR package for processing physical activity data derived from the accelerometer.

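### The planned group × time effect is the plain difference in mean change, so the reported differences are not adjusted for baseline; adjusting would be a free improvement of uncertain size

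*Protocol article*

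**What the plan says.** Section 3.9 of the protocol article schedules two assessments: "At both time points, anthropometric measurements, physical fitness, motor competence", activity level and enjoyment are collected before Session 1 and at Session 16.

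Section 3.13.2 sets the model: "All models will include group (intervention vs. control), time (baseline and post-intervention), and their interaction as fixed effects". The covariates are then fixed: "Age and sex will be included as covariates". For clustering, "A random intercept will be specified for school to account for intraclass correlation within clusters". The intervention effect is the interaction, "which represents the differences between groups in changes from baseline (Session 1) to post-intervention (Session 16").

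Section 3.13.4 says how it will be reported: "Results will be presented as adjusted between-group differences in change". Cohen's d is to come from the same adjusted estimates.

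The only other covariates named are parental education, household income and family structure in section 3.9.2.6: "These variables will be used to characterize the sample and will be considered covariates in the statistical analyses". Nowhere does the article enter the pupil's baseline score as a covariate or give the two arms a common baseline mean.

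**The concern.** The baseline score enters the model only as a second outcome row, and the group main effect lets the arms differ freely at baseline. The interaction then subtracts the whole baseline gap, as if every unit of it would persist to the post-intervention test. When the baseline–post correlation is below 1, only part of a chance gap persists.

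Two consequences follow. The estimate usually has more variance than one that conditions on baseline. And, given the gap actually observed, it is displaced in the opposite direction: an intervention arm that starts high by chance looks worse, and one that starts low looks better. Only six classes are randomised, one per arm in each of three schools, so a noticeable chance gap is likely. A reader who sees the word adjusted in section 3.13.4 could also believe that baseline has been dealt with.

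**Working it through.** **Inputs from section 3.2.** Difference 3 points of body fat, SD 5, two-sided alpha 0.05, power 80%, class size 35, ICC 0.03, dropout 15%, three classes and 105 pupils per arm. The baseline–post correlation is not given and is varied below.

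**1. The plan's own figure.** n = 2(1.96+0.84)²·25/9 ≈ 44 per arm. Design effect 1 + 34·0.03 = 2.02. 44·2.02 = 88.9, and 88.9/0.85 = 104.6. The stated 44, 88 and 104 are reproduced.

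**2. What the interaction estimates.** With complete data the fixed effects fit the four group-by-time means freely, so group × time = (post − baseline, intervention) − (post − baseline, control). Age and sex do not differ between a pupil's two rows and enter only as main effects, so they cancel. As a check, the model of section 3.13.2 was fitted to one simulated data set (3 schools × 2 classes × 35 pupils). The interaction was 0.5647 and the raw difference in mean change 0.5647. Baseline adjustment on the same data gave 0.431. This illustrates the identity, not a typical size. Different random effects would not alter the identity in complete, balanced data.

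**3. Precision if class means regress like pupils' scores.** In units of outcome variance, the change contrast has variance proportional to 2(1−rho) and the baseline-adjusted contrast to 1−rho². The ratio is (1+rho)/2: 0.75 at rho 0.5, 0.85 at 0.7, 0.90 at 0.8.

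**4. Precision and shift if class means are more stable than pupils' scores.** Analysed pupils per class: 35·0.85 = 29.75. Per class mean, the class component is B = 0.03 and the pupil component is W = 0.97/29.75 = 0.0326. The SD of the chance baseline gap between arms is sqrt(2(B+W)/3) = sqrt(0.0417) = 0.204 outcome SD. Let r be the pupil correlation (0.5 here) and c the class correlation, with r as the adjustment slope. Up to the common factor 2/3:

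- planned variance = 2[(1−c)B + (1−r)W]
- adjusted variance = B(1+r²−2rc) + W(1−r²)
- share of the gap that persists = (cB + rW)/(B+W)
- shift of the planned estimate for a 1-SD gap = (1 − share)·0.204

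| c | planned | adjusted | ratio | share | shift (SD) |
|---|---|---|---|---|---|
| 0.5 | 0.0626 | 0.0470 | 0.75 | 0.50 | 0.10 |
| 0.9 | 0.0386 | 0.0350 | 0.91 | 0.69 | 0.06 |
| 1.0 | 0.0326 | 0.0320 | 0.98 | 0.74 | 0.05 |

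At c = 1, pupil-level adjustment removes 0.50 of the gap where 0.74 persists, so it under-corrects by 0.24·0.204 = 0.05 SD. That is about as much as the change score over-corrects. Simulations with fully stable classes gave ratios of 0.96 to 1.06 over pupil correlations 0.4 to 0.8.

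**5. Power.** Use 88 per arm, design effect 2.02 and a normal approximation, with correct standard errors. The noncentrality is 3/(5·sqrt(v·2·2.02/88)) = 2.80/sqrt(v).

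- SD 5 as the SD of change: v = 1 planned and (1+rho)/2 adjusted. At rho 0.7 power goes from 80% to 86%.
- SD 5 as the SD of the score: v = 2(1−rho) planned and 1−rho² adjusted. At rho 0.7 power goes from 95.1% to 97.5%.
- At rho 0.5 both readings give 80% to 90%.

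**The case against.** The strongest reply is that this is a choice, not an error. The difference in change is a standard estimator, it is unbiased over randomisation, and sections 3.13.2 and 3.13.4 describe it consistently, with age and sex as the declared adjusters. That stands. A reader might infer that the planned analysis is biased or invalid; the documents do not support that. What remains is avoidable imprecision and a displacement conditional on the observed gap.

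A second reply is that intact classes may be stable, so the gain may vanish. That also stands. With fully stable class effects there is no gain and no material loss, and pupil-level adjustment then leaves an error of similar size in the other direction. It would be too strong to say that the change score always over-corrects while adjustment gets the gap right.

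A third concerns power. One could read step 5 as a rise from 80% to 90%. The documents do not support any single figure: SD 5 is given for body fat, not for the motor competence score that section 3.9.1.1 makes primary, and section 3.2 does not say whether it is the SD of the score or of change. The calculation also presumes correct standard errors, whereas the stated model has a random intercept for school only, with no term for class or pupil. That is a separate and larger matter, which baseline adjustment alone would not cure.

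**Conclusion.** The point holds as a free improvement. The interaction fixed in section 3.13.2 is the plain difference in mean change, and the adjusted differences of section 3.13.4 are not adjusted for baseline. The identity rests on two time points and complete data (or each completed data set after imputation).

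The size depends on two correlations that the protocol does not state. The variance saved runs from about 25% (pupil and class correlation both 0.5) through about 10% (class 0.9, pupil 0.5; or 0.8 at both levels) to essentially nothing with fully stable classes. At pupil correlation 0.5, a typical baseline gap of 0.20 outcome SD displaces the planned estimate by 0.05 to 0.10 SD against the gap. In none of these cases does adjustment carry a material penalty, and the article gives no reason for preferring the free-baseline form.

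**What to change.** In section 3.13.2, for the outcomes measured before and after the intervention (motor competence, fitness, enjoyment, body composition, self-reported activity), make the baseline-adjusted between-group difference the primary estimate. Use one of two forms:

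- regress the post-intervention score on group, the pupil's baseline score of the same outcome, age, sex and school; or
- keep the repeated-measures layout but drop the group main effect, so that both arms share one baseline mean, and model the within-pupil correlation. This form also retains pupils with a single measurement.

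In either form account for class, the randomised unit, and state the small-sample inference to be used. Six classes leave 6 − 2 = 4 class-level degrees of freedom, or 6 − 4 = 2 if school is also fitted as a fixed effect.

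Report that coefficient, and the Cohen's d derived from it, in section 3.13.4, and align the abstract's sentence on the interaction. Keep the change-score contrast as a sensitivity analysis.

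The cost is wording, settled before outcome data are seen. No extra pupils, measurements or staff are needed, and the software already named can fit both forms.

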**Methods:**

A cluster-randomized controlled trial will be conducted among 11- to 12-year-old schoolchildren. Schools will be selected at random, and within each school, two classes from the same grade will be assigned to the intervention or control groups. The intervention will consist of an eight-week instructional unit (16 sessions) based on four alternative sports (flag football, ultimate frisbee, korfball, and kin-ball) taught using the Teaching Games for Understanding approach. The control group will continue with the regular physical education curriculum. Physical fitness, motor competence, and enjoyment of physical activity will be assessed as primary outcomes, while physical activity levels and body composition will be considered secondary outcomes. All variables will be assessed before and after the intervention. Primary analyses will follow the intention-to-treat principle using mixed-effects models to account for clustering (students within schools). The effects of the intervention will be estimated using the group × time interaction. Analyses will be performed using SPSS v28 and R v4.3.

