### Sample size

3.2

The trial is designed as a cRCT with the class group as the unit of randomization. The minimum clinically relevant difference in body fat percentage has been defined as 3 percentage points (*Δ* = 3), with an estimated standard deviation of 5. A significance level of *α* = 0.05 (two-sided) and a statistical power of 80% were assumed. An average group size of *n* = 35 students and a loss-to-follow-up/dropout rate of 15% were considered. Based on recent literature on randomized controlled trials (RCTs) in school-aged children, an intracluster correlation coefficient (ICC) of 0.03 was assumed (18).

With these assumptions, approximately 44 students per group are needed in a single trial. Adjusting for the cluster effect with an ICC = 0.03, the group size increases to approximately 88 students. Therefore, considering a 15% attrition rate, the final group size is approximately 104 students. To achieve this with groups of an average size of 35, 3 courses/groups per cohort (6 groups in total) will be required, implying 210 enrolled students (105 in the intervention group/105 in the control group). The flow of participants throughout the study is summarized in Figure 2.

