### Randomization and blinding

3.3

Randomization will be conducted at the school and class levels. Urban schools in the city of Talca, Chile, will be randomly selected using a computer-generated sequence. Three schools will be included, representing different administrative types within the Chilean education system: a public school, a subsidized private school, and a private school.

Within each participating school, two intact classes will be included. One class will be randomly assigned to the intervention group (IG) and the other to the control group (CG), resulting in parallel groups within the same educational setting.

Due to the nature of the school-based intervention, it will not be possible to blind participants, teachers, and intervention staff. However, data management and statistical analyses will be conducted using anonymized datasets to minimize potential bias.

To ensure treatment fidelity and minimize experimenter bias, the intervention will be implemented by an external researcher who is specialized and specifically trained in the study protocol (29). In contrast, the control group will maintain its usual curriculum as led by the school’s regular teacher. This design not only allows for rigorous standardization of the independent variable but also ensures that the control group reflects real-world conditions, thereby preserving the ecological validity of the study in naturalistic school settings (30, 31).

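### The primary model puts its only named random effect on school, where it cancels from group × time; the class-level drift and student pairing that set the true standard error are not modelled

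*Protocol article*

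**What the plan says.** Section 3.2 (Sample size) fixes the randomised unit: "The trial is designed as a cRCT with the class group as the unit of randomization". It applies an ICC of 0.03 to classes averaging 35 students and arrives at six classes and 210 students. Section 3.3 (Randomization and blinding) says "Three schools will be included" and that within each one "One class will be randomly assigned to the intervention group (IG) and the other to the control group (CG"). Section 3.9 adds the repeated measures: "Assessments will be conducted at two time points".

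The analysis text describes a different structure. The abstract speaks of "mixed-effects models to account for clustering (students within schools"), and section 3.13.2 uses the same nesting. That section estimates the effect through group × time. For all models it lists group, time and their interaction as fixed effects with age and sex as covariates, and then states "A random intercept will be specified for school to account for intraclass correlation within clusters". Section 3.13.3 reuses this model for the per-protocol analysis. No class, class-by-time or student term is named anywhere in the article.

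**The concern.** The term given the job of handling the clustering cannot do it. Each school contributes one intervention and one control class, so a school intercept shifts both arms and both time points equally and disappears from the difference in changes. What remains is a model that treats all baseline and post scores within a school as independent.

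Two features of the data then go unaccounted for, with opposite effects on the standard error of group × time:

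- **Class-by-time variation** (a class drifting between tests for reasons unrelated to treatment) is left out, which makes the standard error too small.
- **The student effect**, and any class effect that is constant over time, cancels from the true contrast but is pushed into the model's residual, which makes the standard error too large.

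The planned standard error responds to neither quantity. At stake are the confidence interval and p-value of every outcome analysed with this model, including motor competence, which section 3.9.1 names as primary.

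**Working it through.** **The plan's own figure.** With Δ = 3, SD = 5, two-sided α = 0.05 and 80% power, n per arm = 2 × (1.960 + 0.842)² × 25/9 = 43.6, so 44. The design effect is 1 + (35 − 1) × 0.03 = 2.02, and 44 × 2.02 = 88.9 (the article says about 88). Then 88/0.85 = 103.5, so 104, and three classes of 35 give 105 per arm. The figures reproduce, and they treat the class as the cluster, unlike the analysis model.

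**Inputs.** Three schools, two classes per school and two time points (protocol). Analysed class size m = 35 with no dropout, or about 30 after 15% loss (35 × 0.85 = 29.75). The within-student correlation and the stability of class effects over time are not given. I set the within-school variance to 1 and assume residual variance σ²e from 0.2 to 0.5 and class-by-time variance σ²ct from 0 to 0.03. The upper end is the ceiling implied by the stated ICC, because the part of the class variance that changes over time cannot exceed the total class variance.

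**Formulas.** The group × time estimate averages, over three schools, the difference between two class mean changes. Each class mean change has variance 2σ²e/m + 2σ²ct, so

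- true variance = (4/3m)(σ²e + m·σ²ct)
- variance under the school-only model = (4/3m) × 1
- type I error at nominal 5% = 2 × [1 − Φ(1.96 × planned SE / true SE)]

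The planned SE is √(4/90) = 0.211 for m = 30 and √(4/105) = 0.195 for m = 35, whatever σ²e and σ²ct are.

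**Results** (first value σ²e = 0.2, second 0.5):

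| σ²ct | True SE, m = 30 | Type I error, m = 30 | True SE, m = 35 | Type I error, m = 35 |
|---|---|---|---|---|
| 0 | 0.094, 0.149 | <0.1%, 0.6% | 0.087, 0.138 | <0.1%, 0.6% |
| 0.015 | 0.170, 0.206 | 1.5%, 4.4% | 0.166, 0.198 | 2.1%, 5.3% |
| 0.03 | 0.221, 0.249 | 6.2%, 9.8% | 0.218, 0.243 | 8.0%, 11.5% |

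Null simulations with fitted mixed models (300 runs each, 35 per class, ICC 0.03) rejected in 0.00, 0.01 and 0.12 of runs for no, half and full drift, in line with the formula.

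**Adding only a student intercept.** The model's variance becomes (4/3m)(σ²e + σ²ct), which still omits the factor m on class drift. At σ²ct = 0.03 and m = 30, the ratio of true to model SE is √(1.1/0.23) = 2.19 for σ²e = 0.2 and √(1.4/0.53) = 1.63 for σ²e = 0.5. Type I error is then about 37% and 23%.

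**Power of a class-level test.** With school as a stratum there are 6 − 3 − 1 = 2 degrees of freedom and the critical value is 4.303. The planned effect is 3/5 = 0.6 SD. Using a non-central t with non-centrality 0.6/true SE, change-score power is 57-91% at σ²ct = 0 and 28-34% at 0.03.

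**The case against.** The best counter-argument is that the article names a school intercept without saying it is the only random term. It calls the design repeated-measures, so a fuller plan could include a student effect, and degrees of freedom are routinely left to such a plan. That stands in part. I make no finding of the article's silence on degrees of freedom, and the student term could yet appear. The level of clustering is different: the article states it, gives the school intercept the task of handling it, and repeats the nesting in the abstract. An analysis plan would have to contradict this text to correct it.

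A reader might infer that the planned test is simply anti-conservative, with false-positive rates of 14-32%. The documents do not support that. Such rates need class-by-time variance of 0.05 to 0.10, above the total class variance implied by an ICC of 0.03. Within the protocol's own assumption the test is conservative over most of the range, and the error is at most roughly doubled, at the ceiling. That ICC was chosen for body fat, however, and the article gives none for motor competence.

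A reader might also infer that leaving out any class effect makes this standard error too small. A class effect that is constant over time cancels from group × time, so leaving it out has the opposite effect. Only drift makes the standard error too small.

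**Conclusion.** The model in section 3.13.2 is wrong as written: its named random effect sits at the level of the stratum, not at the level randomised, and it contributes nothing to the precision of group × time. The reported intervals and p-values will not have their nominal properties, and the article does not allow the direction of the error to be predicted. Under the assumptions above, type I error lies between about 0% and 12%. The two omissions can nearly cancel (4.4-5.3% at σ²ct = 0.015 with σ²e = 0.5), but nothing in the design ensures that. These figures assume equal class sizes and rest on assumed residual and drift variances. The mismatch between class randomisation and school-level modelling rests on no assumption.

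**What to change.** In section 3.13.2 and the abstract, describe the data as students within classes within schools and make the inference at class level. Either of these would do:

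- Model the post score on arm, baseline score, age, sex and school as a fixed three-level stratum, with a random intercept for class.
- Keep group × time, with random effects for student, class and class-by-time, and with school and school-by-time as fixed terms so that school acts as a stratum for change.

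In both cases fix the test at 2 class-level degrees of freedom in advance, so that a class variance estimated as zero does not return the test to student-level degrees of freedom. Do not add a student intercept alone. Include class in the imputation model, and use the same structure for the per-protocol analysis in section 3.13.3.

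No extra data are needed for the new wording, but it has a real cost: intervals will be wider whenever classes drift, and the 2-df critical value lowers power. The claim of more than 80% power in section 3.2 should be restated with the ranges above. Comparing the six class mean changes without the school stratum gives 6 − 2 = 4 degrees of freedom and somewhat more power (about 45-55% at σ²ct = 0.03), but gives up the pairing within which classes were randomised. The shortage of power comes from having six classes, and the choice of model cannot remove it.
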